## Assignment of interventions: blinding

### Who will be blinded {17a}

Evaluators will be blinded to the randomization and intervention processes; they will be responsible only for the evaluation procedures and will not receive information about the assignment of individuals to groups. Participants and the principal researcher responsible for the treatment will not be blinded due to the nature of the interventions.

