**Methods:**

This is a 2-arm, randomized, placebo-controlled trial with blinded evaluators. The research will be carried out in the laboratory of physical agents at the Andrés Bello University, Campus Casona de las Condes. Eligible participants include the entire internal and external community associated with Andrés Bello University suffering from chronic non-specific NP. Participants will be stratified by sex (4 subgroups) and randomized into 2 study groups: group 1 (HILT and stretching exercises) and group 2 (sham HILT and stretching exercises). Treatments will be performed twice a week for 4 weeks with 3 assessments: before treatment (T0), at the end of treatment (T1), and 12 weeks after treatment (follow-up) (T2). The main outcomes will be pain intensity at rest, pain intensity at movement (active cervical movements: flexion, extension, right and left side bending, and right and left rotation), and pain pressure threshold (average obtained for six evaluation points). Secondary outcome measures will include neck range of motion in the sagittal, coronal, and transverse planes and neck disability.

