### Trial design {8}

This is a 2-arm randomized placebo-controlled superiority trial (RCT) with patient and evaluator blinded to the group allocation. This study is reported in accordance with established clinical trial reporting standards: the Consolidated Standards of Trial Reporting (CONSORT). The protocol was developed following the recommendations of Standard Protocol Elements: Recommendations for Interventional Trials (SPIRIT).

The study has been approved by the Ethics Committee of the Eastern Metropolitan Health Service (SSMO), Santiago de Chile, following the Helsinki principles (approval date: October 26, 2022. N° 20200234) [23].

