## Interventions

### Explanation for the choice of comparators {6b}

HILT’s studies on CNNP are limited and done without using a placebo control. In this study, HILT will be compared with a sham HILT application. Placebo comparators are considered the gold standard for evaluating the efficacy of an intervention in clinical trials. This will allow assessing the analgesic efficacy of HILT as well as its effect on other variables like cervical ROM and neck disability.

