#### Sham high-intensity laser application (HILT) — control group

For sham HILT intervention, individuals will be treated with the same care as the current intervention group, including dose, therapy time, individual care, and the physical space where the therapy will be performed. The placebo intervention will be performed as a control.

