### Implementation {16c}

Four independent physical therapists will work on this study, and each of them will have a specific role. The principal researcher (R1) will oversee participant recruitment, participant registration, randomization, and the random allocation sequence. Moreover, the interventions will be implemented by a researcher (R2) (HILT, sham HILT, and exercise). All evaluations will be performed by a third researcher (R3) (RPI, MPI, PPT, CROM, and ND). The principal researcher will examine and record the data.

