### Plans to promote participant retention and complete follow-up {18b}

Principal researcher (R1) and an evaluator (R2) will be responsible for notifying and monitoring the participants on a weekly basis (via telephone contact, WhatsApp, and/or email) and accompanying them during the research.

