## Discussion

The World Association for Laser Therapy (WALT) has proposed dosing recommendations for LLLT therapy in various musculoskeletal conditions; however, no recommendations for HILT have been documented [15, 20, 43]. HILT is a recent resource that has been incorporated into physical therapy for the management of musculoskeletal pain. Trials are emerging suggesting that HILT could decrease pain in conditions such as rheumatoid arthritis, osteoarthritis, low back pain, and NP, but the number and quality of studies are limited. An advantage of HILT over low-intensity lasers (class IIIb) is that it combines the photobiomodulation effects with those of deep thermotherapy, reaching greater depths for its wavelength [15, 20].

This randomized controlled trial will investigate the effect of HILT in patients with non-specific chronic NP and contribute new evidence that is currently limited. This study has a high-quality design that results in high-quality evidence that can be used to compare the analgesic efficacy and effectiveness of HILT to a placebo. In addition, effects can be evaluated if their effects transcend improvements in the range of movement and improved functionality.

The HILT group is expected to obtain significant analgesic differences in terms of a higher pain pressure threshold and lower pain intensity during movement, as well as a greater cervical range of motion and less disability at the end of treatment compared to the control group (sham HILT).

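### The trial design section says patients are blinded and the blinding section says participants are not; the two must be reconciled, because the placebo-efficacy claim depends on which is true

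*Protocol article*

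**What the plan says.** All references are to the protocol article.

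- **Trial design {8}:** a two-arm placebo-controlled superiority trial "with patient and evaluator blinded to the group allocation".
- **Who will be blinded {17a}:** evaluators are blinded, but "Participants and the principal researcher responsible for the treatment will not be blinded due to the nature of the interventions".
- **Abstract, Methods:** "This is a 2-arm, randomized, placebo-controlled trial with blinded evaluators". It does not mention participants.
- **Explanation for the choice of comparators {6b}:** the sham is justified because earlier HILT studies in this condition lacked a placebo control: "Placebo comparators are considered the gold standard for evaluating the efficacy of an intervention in clinical trials".
- **Sham high-intensity laser application:** "individuals will be treated with the same care as the current intervention group, including dose, therapy time", in the same physical space.
- **Discussion:** the trial is presented as able to "compare the analgesic efficacy and effectiveness of HILT to a placebo".

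On roles, Implementation {16c} says "the interventions will be implemented by a researcher (R2) (HILT, sham HILT, and exercise"). It gives all outcome evaluations to R3, and recruitment, randomization and the allocation sequence to the principal researcher, R1. Plans to promote participant retention {18b} says "Principal researcher (R1) and an evaluator (R2) will be responsible for notifying and monitoring the participants on a weekly basis".

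**The concern.** Section {17a} is where a reader, a monitor or a systematic reviewer looks to find out who is blinded, and it contradicts the design statement in {8} on participants.

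A sham controls for expectation only while participants do not know which device they received. Matching for care, time and setting does not replace that. Blinding the evaluator does not repair the loss either, because on these outcomes the evaluator writes down what the participant says or signals. If participants know their arm, a difference between arms could reflect the laser, the belief in it, or both, and the data could not tell these apart. The stated purpose of the comparator would then not be met.

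**Working it through.** **1. The two statements side by side.**

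| Section | Participants | Evaluators |
|---|---|---|
| Trial design {8} | blinded | blinded |
| Who will be blinded {17a} | not blinded | blinded |
| Abstract | not mentioned | blinded |

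Sections {8} and {17a} disagree about the same people. The abstract is compatible with either. The reason given in {17a}, the nature of the interventions, fits poorly with a sham matched to the active procedure, but no sentence withdraws it.

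**2. Which outcomes depend on the participant's report.**

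- Pain at rest and on movement: ratings on the 0 to 10 numerical scale, reported by the participant.
- Pressure pain threshold: the pressure at which the participant reports pain.
- Neck Disability Index: a questionnaire on symptoms and daily activities.

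The first two items and the pressure threshold are the main outcomes in Outcomes {12}; the Neck Disability Index is secondary.

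**3. Illustration of size.** The article gives no figure for blinding, so there is none to reproduce. From Sample size {14} I take only 36 per group (total 72) and d = 0.6. That 36 does reproduce from d = 0.6, power 0.80 and α = 0.05, but with a one-sided t-test (35.04, rounded up). This is a separate matter and does not bear on blinding.

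Assumptions that are not in the article: SD of the pain score 1.5, 2 or 2.5 points; a pure reporting shift of 0.5 or 1.0 point in favour of HILT; no laser effect; two-sided α = 0.05.

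Degrees of freedom = 36 + 36 − 2 = 70. Critical value t(0.975, 70) = 1.994.

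Noncentrality = (bias / SD) × √(36/2) = (bias / SD) × 4.243.

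Rejection probability = P(|T| > 1.994), with T noncentral t on 70 df.

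| SD | Bias 0.5: noncentrality | Bias 0.5: P(p<0.05) | Bias 1.0: noncentrality | Bias 1.0: P(p<0.05) |
|---|---|---|---|---|
| 1.5 | 1.414 | 29% | 2.828 | 80% |
| 2 | 1.061 | 18% | 2.121 | 55% |
| 2.5 | 0.849 | 13% | 1.697 | 39% |

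For scale, the planned effect is 0.6 × SD: 0.9, 1.2 and 1.5 points respectively. A bias of 0.2 point at SD 2 (noncentrality 0.424) gives 7%, close to the nominal 5%. The size therefore depends entirely on the assumed bias.

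**The case against.** **It may be only a wording error.** Trial design {8}, the rationale in {6b} and the matched sham all suggest that participants are meant to be blinded, and no sentence says that they are told their arm. This stands as far as it goes. A reader might infer from {17a} that the sham is certainly unblinded and has lost its purpose. The article does not support that: the loss follows only if {17a} is what is done. Equally, {17a} cannot be dismissed as a slip, since it gives a reason and the abstract claims only evaluator blinding.

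**Evaluator blinding.** A reader might also infer that this is broken, because {18b} calls R2 an evaluator while {16c} has R2 deliver both laser and sham. The article does not support that either. Section {18b} concerns reminders and contact, {16c} gives every outcome assessment to R3, and {17a} keeps allocation from evaluators. What remains is a wrong role label.

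**The percentages.** They rest on an SD and bias sizes that the article does not give. They show what a given bias would do, not that it would occur. The contradiction stands without them.

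**Consent wording.** Consent pages are not part of the text reviewed, so what participants are told cannot be judged from it.

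**Conclusion.** The contradiction between {8} and {17a} is established from the text alone, and it must be corrected whichever statement is true.

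Its consequence is conditional. If participants are in fact kept unaware, {17a} is a drafting error and the sham keeps its role. If they know their arm, the efficacy claim in {6b} and in the Discussion is not supported on any main outcome or on disability. In that second case, under the assumed SDs of 1.5 to 2.5, a bias of 0.5 to 1.0 point would produce a nominally significant result in about 13% to 80% of trials with no laser effect, against the intended 5%.

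**What to change.** First establish what is actually done. Recruitment was planned from April 2023, so if participants have already been told their arm, new wording cannot restore blinding.

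- **If participants are kept unaware of their arm:** rewrite {17a} to say that participants and the outcome evaluator (R3) are blinded, and that the treating researcher (R2) and the researcher who holds the allocation sequence (R1) are not.
- **If participants know their arm:** delete the patient-blinding claim in {8}, and limit the conclusion in {6b} and the Discussion to HILT versus an unblinded sham, not efficacy against placebo.

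Two minor role corrections apply in either case. Remove the label of evaluator from R2 in {18b}. Reconcile {17a}, which makes the principal researcher responsible for treatment, with {16c}, which gives treatment to R2.

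Optionally, ask participants at the end of treatment which arm they think they were in, and report the answers by arm. This is an inexpensive check, not a condition for resolving the point.

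The cost is a few sentences of protocol text, plus one question if the optional check is adopted. In the second case there is a further cost: a narrower claim.

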### Procedure for unblinding if needed {17b}

The evaluators will not be allowed to unblock the blinding.

## Data collection and management

### Plans for assessment and collection of outcomes {18a}

All the data will be collected weekly, saved in a Microsoft Excel spreadsheet, and stored on the institutional Portal Office 365 cloud (Andrés Bello University, UNAB). During the development of this research, the data will be restricted and for the exclusive use of registered researchers and participants. All confidential participant data will not be available to the public.

### Plans to promote participant retention and complete follow-up {18b}

Principal researcher (R1) and an evaluator (R2) will be responsible for notifying and monitoring the participants on a weekly basis (via telephone contact, WhatsApp, and/or email) and accompanying them during the research.

### Data management {19}

The principal researcher (R1) will be responsible for the data management.

### Confidentiality {27}

All the information generated during the study will be anonymized, that is, coded without revealing personal data, and handled confidentially. Only the principal researcher will have access to it, and he will keep all the data safe. The data will be stored on the institutional platform (Andrés Bello University), which will be accessible via the institutional Office 365 cloud. Only researchers from the UNAB who participate in this research will have the authorization to access these stored documents.

### Plans for collection, laboratory evaluation, and storage of biological specimens for genetic or molecular analysis in this trial/future use {33}

N/A. Not applicable to this clinical trial.

## Statistical methods

### Statistical methods for primary and secondary outcomes {20a}

The descriptive statistics for the variables RPI, MPI, PPT, CROM, and ND will be used as analysis measures: averages and standard deviation (*x*, SD), median and interquartile range (mean, IQR), depending on the distribution of the data (test of Kolmogorov–Smirnov normality). From these data, a table will be constructed with the demographic data of the participants by group. The secondary variables sex and body mass index (BMI) will be presented with frequencies and averages or medians, respectively, according to the analysis of the normality of the data. For the inferential statistical analysis of the outcome measures, the Kolmogorov–Smirnov normality test and the Bartlet test will be used to determine the distribution of the variables PPT, RPI, MPI, CROM, and ND, and the corresponding homoscedasticity of the variances obtained for these variables in the evaluations (T0, T1, and T2). According to the results, parametric or non-parametric tests will be selected: the changes in the measurement variables within and between groups will be analyzed with the two-factor ANOVA or the Kruskal–Wallis test, depending on the distribution of the data. Subsequently, a post hoc analysis will be carried out with the Tukey or Bonferroni test, depending on the statistical differences. The significance level for all statistical tests will be set at 0.05. Data will be analyzed using IBM Statistical Package for the Social Sciences (SPSS) software (version 26; SPSS Inc.; Chicago, IL) by an investigator who is blind to group assignment.

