### Objectives {7}

The main purpose of the research is to investigate whether pain intensity will decrease after HILT treatment compared with sham HILT after treatment and with a 3-month follow-up. Additionally, secondary outcomes such as changes in pain pressure threshold, active cervical range of motion (flexion, extension, left- and right-side bending, and left and right rotation), and cervical disability will be evaluated. The hypothesis of the study is that HILT will lead to greater pain intensity improvement than conventional treatment. The purpose of this article is to describe the methods and statistical analysis of this study so that this information can be made public.

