### Intervention description {11a}

Participants will be divided into two main groups: group 1 (HILT) and group 2 (sham HILT). Within each group, there will be two subgroups for men and women, determined through a simple randomization process and stratification by sex, utilizing the research randomizer program [25]. his allows the researchers to analyze the outcomes of interest by group and by subgroup. This study recognizes the superior benefits of passive stretching for flexibility improvement, post-exercise recovery, and range of motion limitations, especially in CNNP patients [26–29]. Both groups will receive as a base treatment a bilateral passive stretching exercise plan of the upper trapezius muscle, levator scapulae, and scalenes in 3 series for 30 s [27, 28]. Treatments will be performed twice a week for 4 weeks with 3 assessments: before treatment (T0), at the end of treatment (T1), and 12 weeks after treatment (follow-up) (T2).

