### Sample size {14}

The sample size was determined with the G-Power program using a power of 0.80 (1-*β*), a reliability of 95%, an error of 5% (*α*), and an effect size of *d* = 0.6 (Cohen’s *d*) with reference to previous studies that determined differences in mean pain intensity between experimental and control groups after HILT treatment with effect sizes of 0.53 [30, 40]. Based on the above, the calculated sample size is 72 subjects, with at least 36 subjects per group. The study will include 84 participants (42 per group) in recognition of the crucial role of sample size in determining the power and impact of the study. An additional 15% of participants were considered for possible losses during the follow-up (bias due to abandonment). This is consistent with what the literature recommends, which suggests including at least 10% more participants, and with the PEDro scale (criterion 8), which advocates for analyzing at least 85% of the data to maintain data validity and obtain more robust statistical results and analysis [41, 42].

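### The HILT-versus-sham contrasts at T1 and T2 are not named as the deciding tests, and the post hoc step that appears to supply them has an unstated family and a correction chosen from the results

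*Protocol article*

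**What the plan says.** Objectives {7} sets the question: to "investigate whether pain intensity will decrease after HILT treatment compared with sham HILT after treatment and with a 3-month follow-up". That is two between-group differences per pain outcome, one at each post-baseline visit. Sample size {14} rests on a single two-group difference in mean pain (d = 0.6, 5% error, power 0.80) and arrives at 36 per group, raised to 42 for losses.

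Statistical methods {20a} first checks normality and homogeneity of variance at T0, T1 and T2. It then states that "the changes in the measurement variables within and between groups will be analyzed with the two-factor ANOVA or the Kruskal–Wallis test", depending on the distribution. After that, "a post hoc analysis will be carried out with the Tukey or Bonferroni test, depending on the statistical differences". Finally, "The significance level for all statistical tests will be set at 0.05". The section does not say which model term or visit decides, or which comparisons the post hoc correction covers. The analysis is to be done "by an investigator who is blind to group assignment".

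**The concern.** The printed rule for the correction makes it depend on the differences found, so the threshold for a comparison is settled after the data have been looked at. The contrasts that answer the trial's question are not singled out from the other comparisons that a group-by-time layout offers: changes within each arm, the baseline comparison, and pairs that cross both arm and visit.

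Two things are at stake. First, the same p-value for HILT versus sham could count as significant or not, according to how many other comparisons are taken to share its family. Second, a sample size built for one comparison does not support a test that shares its error rate with many. The problem arises for a single, normally distributed outcome, so it is separate from the number of main outcomes and from the normality pre-test.

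**Working it through.** **Inputs.** From Sample size {14}: d = 0.6, α = 0.05, power 0.80, 36 per group calculated, 42 per group planned. From Intervention description {11a}: two arms and three assessments. Sidedness is not stated in either section.

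**The plan's own figure.** For a two-sample t-test with n per group, df = 2n − 2 and the non-centrality is d√(n/2). With n = 36 this is 0.6 × √18 = 2.546 on 70 df.
- One-sided 0.05: power 0.809, and 36 is the smallest n that reaches 0.80. The total of 72 is reproduced exactly.
- Two-sided 0.05: power 0.709. Reaching 0.80 needs 45 per group, 90 in total.

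The stated size therefore matches one uncorrected, one-sided comparison.

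**What the ANOVA terms deliver.** I take the two factors as group and time, which the section implies but does not state.
- Group main effect: it averages the HILT-minus-sham difference over T0, T1 and T2. Baseline can carry no treatment effect. A constant effect δ at T1 and T2 therefore becomes (0 + δ + δ)/3 = 2δ/3, and an effect at T1 alone becomes δ/3.
- Group-by-time interaction: it has (2 − 1)(3 − 1) = 2 df and does not identify a visit.

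Neither term is the difference at T1 or at T2. A group factor with two levels also needs no pairwise correction of its own, so Tukey or Bonferroni has work to do only across visits or group-by-time cells.

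**Size of the open family.** Two arms × three visits give 6 cells and 6 × 5/2 = 15 pairs, of which only two are HILT versus sham after baseline. As the family is not stated, I show a range. Bonferroni thresholds are 0.05/k. For Tukey, the 5% studentized range for 6 means on 210 df is 4.068, so the critical t is 4.068/√2 = 2.876, a per-pair two-sided p of 0.0044. Power is from the two-sided non-central t at d = 0.6.

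| Assumed family | Threshold | Power, 36/group | Power, 42/group | Smallest significant observed d, 36/group |
|---|---|---|---|---|
| One planned contrast | 0.05 | 0.709 | 0.776 | 0.47 |
| Bonferroni, T1 and T2 | 0.025 | 0.602 | 0.679 | 0.54 |
| Bonferroni, 9 (3 between, 6 within) | 0.0056 | 0.383 | 0.465 | 0.67 |
| Tukey, all 15 pairs | 0.0044 | 0.355 | 0.435 | 0.69 |
| Bonferroni, all 15 pairs | 0.0033 | 0.320 | 0.398 | 0.72 |

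In the last three rows, with 36 per group, the observed effect would have to exceed the assumed 0.6 to be significant. If changes from baseline were analysed instead, there would be 4 cells and 6 pairs. Bonferroni would then give 0.05/6 = 0.0083, inside the range shown.

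**Size of the Tukey-or-Bonferroni choice alone.** Over the same 15 pairs it moves the threshold only between 0.0033 and 0.0044. A simulation with no effects, 36 per group and uncorrelated visits gave a family-wise error of 0.052 for Tukey, 0.040 for Bonferroni and 0.052 if either may be used.

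**The case against.** **Between-group changes are tested directly.** A reader might infer that HILT versus sham can be reached only through a post hoc test. The text does not support that. It assigns between-group changes to the ANOVA or Kruskal–Wallis test itself. The ANOVA has a group term and normally an interaction, and a two-group Kruskal–Wallis at one visit is the HILT-versus-sham test. What stands is narrower: the visit-specific contrasts are not named, and in the ANOVA branch they appear to come from the post hoc step.

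**The choice of correction does little harm.** This is right. A reader might blame the whole span from 0.0033 to 0.05 on Tukey versus Bonferroni, but almost all of it comes from the unstated family.

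**The family is detail for an analysis plan that is not shown.** On its own, that would be a fair answer. But the article prints a rule that ties the correction to the results, and Objectives {7} says the article is meant to set out the statistical analysis.

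**The sentence has milder readings.** Tukey might follow the ANOVA and Bonferroni the Kruskal–Wallis test, or post hoc tests might be run only where the first test finds a difference. Either is possible. Neither is written, and neither names the contrast or the family.

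**The analyst is blinded.** This hides the arm labels and so limits steering towards HILT. It does not hide the size of differences or the p-values.

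**Within-group tests are harmless if not misused.** A reader might infer that a significant fall in the HILT arm will be offered as evidence of efficacy. The document does not say so: the objective and the expected results are both framed against sham. I therefore put no figure on that risk.

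**Conclusion.** The point holds in limited form. Section {20a} does not make the two contrasts asked for in Objectives {7} the deciding tests, and it sets a results-dependent choice of correction over a family that it does not define. The choice of correction is minor in itself. The open family is the larger matter, with power for HILT versus sham falling to about half of its single-contrast value, or slightly less, at the strict end.

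This range rests on three assumptions: the family could be as small as one contrast or as large as all 15 cell pairs; the six cells are treated as independent for Tukey, although visits come from the same people; and tests are two-sided. The strict end errs on the conservative side, so loss of power and a favourable choice of family are alternative risks, not joint ones. The 71% starting point reflects the one-sided sizing and not the post hoc step. Whether the corrected comparison was ever meant to span all pairs cannot be settled from the document.

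**What to change.** In {20a}:
- Delete the results-dependent choice between Tukey and Bonferroni.
- For each outcome, make the planned HILT-minus-sham contrasts at T1 and T2 the deciding tests, preferably baseline-adjusted and with 95% confidence intervals. Estimate them directly from the model, with no omnibus test as a gate.
- Fix one rule for the two time points in advance. Testing T1 and then T2 in sequence, or Bonferroni at 0.025 each, are both acceptable. Objectives {7} does not rank the visits, so the choice is the sponsor's.
- Describe the visits in words as well as by label, because Outcomes {12} calls the same two visits T2 and T3.
- Report within-group changes descriptively, as means with confidence intervals.

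This takes a few sentences and no new data. It has two costs. Within-group p-values are no longer presented as results. The stated 80% power is also not met by a two-sided 0.05 test: it is 71% at 36 per group and 78% at 42, or 60% and 68% under Bonferroni at 0.025. The plan should disclose this. Baseline adjustment may recover some of it, by an amount that depends on a correlation the document does not give.
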